## Abstract

**Background:**

Preterm birth and very small size at birth have long-term effects on neurodevelopment and growth. A relatively small percentage of extremely low birthweight babies suffer from severe neurological disability; however, up to 50 % experience some neurodevelopmental or learning disability in childhood. Current international consensus is that increased protein intake in the neonatal period improves both neurodevelopment and growth, but the quantum of protein required is not known. This trial aims to assess whether providing an extra 1 to 2 g.kg^-1^.d^-1^ protein in the first 5 days after birth will improve neurodevelopmental outcomes and growth in extremely low birthweight babies.

**Methods/Design:**

The ProVIDe study is a multicentre, two-arm, double-blind, parallel, randomised, controlled trial. In addition to standard intravenous nutrition, 430 babies with a birthweight of less than 1000 g who have an umbilical arterial line *in situ* will be randomised in 1:1 ratio to receive either an amino acid solution (TrophAmine®) or placebo (saline) administered through the umbilical arterial catheter for the first 5 days. Exclusion criteria are admission to neonatal intensive care more than 24 h after birth; multiple births of more than 2 babies; known chromosomal or genetic abnormality, or congenital disorder affecting growth; inborn error of metabolism, and in danger of imminent death.

*Primary outcome:* Survival free from neurodevelopmental disability at 2 years’ corrected age, where neurodevelopmental disability is defined as cerebral palsy, blindness, deafness, developmental delay (standardised score more than 1 SD below the mean on the cognitive, language or motor subscales of the Bayley Scales of Infant Development Edition 3), or Gross Motor Function Classification System score ≥1.

*Secondary outcomes:* Growth, from birth to 36 weeks’ corrected gestational age, at neonatal intensive care discharge and at 2 years’ corrected age; body composition at 36 to 42 weeks’ corrected postmenstrual age and at 2 years’ corrected age; neonatal morbidity, including length of stay; nutritional intake.

**Discussion:**

This trial will provide the first direct evidence of the effects of giving preterm babies a higher intake of intravenous protein in the first week after birth on neurodevelopmental outcomes at 2 years corrected age.

**Trial registration:**

Australian New Zealand Clinical Trials Registry: ACTRN12612001084875.

## Background

Advances in neonatal intensive care mean that the majority of preterm babies, even at the extremes of gestation, now survive infancy, childhood and adolescence [1]. The ultimate goal for neonatal care is optimal growth, neurodevelopment and long-term health for survivors [2]. A relatively small percentage of preterm babies suffer from severe neurological impairment; however, up to 50 % of extremely low birthweight (ELBW; birthweight <1000 g) babies experience some neurodevelopmental or learning impairment in childhood [3]. Current international consensus is that increased protein intake in the neonatal period improves neurodevelopment, growth, and body composition, but the quantum of protein required is not known. Therefore, it is now crucial that fundamental elements of neonatal nutrition care, such as the protein intake required for optimal growth and how this influences neurodevelopment and long-term health for preterm babies, are addressed.

The fastest rate of postnatal growth in the human lifecycle is (potentially) that of a preterm baby between 23 and 27 weeks’ gestation when weight gain is approximately 21 g.kg^-1^.d^-1^ [4]. However, faltering growth at the equivalent gestational age is common in preterm babies [5, 6], due to the difficulties in providing nutrition sufficient to support this rate of growth [6, 7]. Preterm babies frequently suffer both fetal and postnatal growth restriction leading to a different pattern of postnatal weight gain and body composition, including lower length at term-equivalent age, lower lean muscle mass, and higher total body fat mass [6, 8–10]. Each of these patterns of growth is associated with an increased risk of adult disease [11–13] and both fetal growth restriction and postnatal faltering growth also are associated with adverse neurodevelopmental outcome [14, 15].

Suboptimal nutrition likely contributes to both the faltering postnatal growth and impaired neurodevelopmental outcomes that are seen commonly in ELBW babies [16, 17]. In preterm babies, length and head growth appear to be affected early, in contrast to the classic faltering growth of poorly nourished term infants, with Z-scores falling by 1–2 standard deviations for all measures of growth during the first month of postnatal life [18, 19]. This early effect on head growth likely reflects the extremely rapid brain growth that occurs at the gestational ages ELBW babies are receiving suboptimal nutrition, as head circumference correlates with brain volume [20]. Volumetric magnetic resonance imaging (MRI) analyses suggest that cerebellar surface area increases 30-fold in the last 16 weeks of pregnancy and cerebral cortical volume increases four-fold from 28 to 40 weeks’ gestational age [21–23]. This very rapid development may also result in greater vulnerability to damage from less than optimal nutrition. Indeed, in adolescents born preterm, performance in final school exams and intelligence quotient (IQ) score are best predicted by the total volume of white matter in the brain detected on MRI scans, irrespective of the presence or severity of other brain abnormalities [24], with 70 % of the variance in IQ explained by total white matter volume and the cross-sectional area of the corpus callosum [24].

Thus, a key modifiable factor for improving neurodevelopmental outcome in preterm babies is improving growth, especially head growth, by optimising nutritional intake in the early postnatal period. Retrospective data suggest that, across a range of protein intakes that were below international recommendations, each 1 g.kg^-1^.d^-1^ increase in protein intake in the first week after birth in ELBW babies improves Mental Development Index scores by 8 points on a Bayley II assessment at 18 months [25]. However, not all data are consistent in this regard [26], few data are from robust randomised controlled trials and even fewer data are from studies in which protein and other nutrient intakes met international recommendations.

We previously have reported that babies with a birthweight of <1200 g failed to meet consensus recommended intravenous nutrient intakes [7, 27–29], consistent with international experience [30, 31], and that this was particularly common in ELBW babies. Close adherence to nutritional guidelines designed to increase nutritional intakes to match international recommendations does result in both increased protein intakes and significantly better growth for weight, length and head circumference, although the benefit for length growth was less than that for weight and head circumference [18]. However, despite these improvements, growth rates are still less than intrauterine growth velocity at comparable gestational ages, the currently accepted recommended goal for ELBW babies [32]. This may be because protein intake in the first week after birth remains less than estimated placental protein uptake *in utero* between 23 and 27 weeks’ gestational age (3.6 to 4.8 g.kg^-1^.d^-1^) [33] and is, therefore, still insufficient to support *in utero* protein accretion rates. Indeed, better linear growth is associated with higher protein intakes in the first week after birth [19]. We, therefore, hypothesise that a higher protein intake during the first week after birth will improve neurodevelopmental outcomes at age 2 years’ corrected age.

In clinical practice, recommended protein intakes are difficult to achieve due to the low fluid volumes administered to ELBW babies during the first week after birth and their need for other infusions containing non-nutritive fluids such as drugs. We propose to utilise the umbilical artery catheter (UAC) to deliver additional protein, substituting the non-nutritive fluids usually given via the UAC with an amino acid solution. This research will fill an urgent need for data from randomised controlled trials investigating the effect of early nutritional practices on clinically important outcomes in these most vulnerable babies.

### Hypothesis

The primary hypothesis is that for ELBW babies, an extra 1 g.d^-1^ of protein in the first 5 days after birth will improve survival free from any neurodevelopmental disability at 2 years’ corrected age. The secondary hypotheses are that increased protein intake in the first week after birth has benefits relating to neonatal morbidity, length of neonatal intensive care unit (NICU) stay, growth and body composition.

### Aims and objectives of this trial

We propose replacing the non-nutritional fluids (saline) that currently are administered via the UAC with an intravenous amino acid solution and will assess the effect of this intervention through a randomised, placebo controlled trial. The aim is to determine whether an additional 1 to 2 g.kg^-1^.d^-1^ protein (amino acid solution) via the UAC starting within 24 h of birth and continued for 5 days will (i) improve survival free of neurodisability at age 2 years’ corrected; (ii) improve body composition, and (iii) prevent faltering growth at NICU discharge.

Specific aims are to determine the effect of the intervention on:Survival free of neurodisability at 2 years’ corrected ageGrowth, from birth to 36 weeks’ postmenstrual age, at NICU discharge and at 2 years’ corrected age.Body composition, at 36 weeks’ postmenstrual age measured by air displacement plethysmography, and at 2 years’ corrected ageNeonatal morbidity, including length of stayNutritional intake

## Methods/Design

### Trial design

Multicentre, double-blind, two-arm, parallel, randomised, controlled trial.

### Ethical approval

The Northern B Health and Disability Ethics Committee has given ethical approval for this study (No 13/NTB/84), and each participating site has institutional approval through local institutional review processes. The New Zealand National Screening Unit has given approval for access to the Newborn Metabolic Screening data.

### Inclusion criteria

Babies with a birthweight of less than 1000 g who have a UAC *in situ* in an acceptable position.

### Exclusion criteria

Babies admitted to neonatal intensive care more than 24 h after birth; multiple births of more than 2 babies; known chromosomal or genetic abnormality, or congenital disorder affecting growth; inborn error of metabolism; in danger of imminent death.

### Trial entry and randomisation

Parents will be given a written information sheet about the study antenatally (where possible), which will be reviewed with them by a member of the study team. If birth occurs without time for this to happen, information will be given to the parents as soon as is feasible after birth and reviewed with them by a member of the study team. Within 24 h of birth and once a UAC has been placed, eligible babies will be randomised to either the placebo group or the intervention group. Babies for whom it was not possible to obtain consent antenatally will be enrolled based on a waiver of consent (approved by the ethics committee) with a requirement that informed, written consent is obtained within 24 h. If consent is not obtained within 24 h of randomisation, the baby will be withdrawn from the study.

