#### Participant withdrawal

Development of significant renal impairment (serum creatinine > 130 μmol.l^−1^) or diagnosis of an inborn error of metabolism requiring prescribed protein intakes will result in the intervention being discontinued. Participants will be withdrawn from the trial at parental request or if the attending physician determines that this is essential for the baby’s care. Consent will be requested to continue to use routinely collected data for study purposes.

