### Study outcomes

#### Primary outcome

The primary outcome will be survival free from any neurodevelopmental disability at 2 years’ corrected age. Assessment will include the Bayley Scales of Infant Development Edition 3 (Bayley III), neurodevelopment, growth and body composition. Cerebral palsy (loss of motor function and abnormalities of muscle tone and power) and other impairment outcomes will be assessed according to previously reported criteria [39]. The severity of gross motor function will be classified using the Gross Motor Function Classification System [40]. Children with severe developmental delay who are unable to complete the psychological assessment will be given a standardised score of - 4 SD. Children will be considered blind if visual acuity in both eyes is worse than 6/60 and deaf if their hearing loss is sufficient to require hearing aid(s), or worse.

Children will be considered to have a neurodevelopmental disability if they have cerebral palsy, a gross motor classification score ≥1 [40], blindness, deafness or developmental delay, defined as a standardised score for cognitive, motor or language scales more than 1 SD below the mean [41]. The neurodevelopmental disabilities imposed by the various neurodevelopmental impairments will be classified as severe, moderate or mild [39].

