#### Statistical considerations

##### Sample size

A total of 430 babies (*n* = 215 in each group) will provide 85 % power at a 5 % level of significance (two-sided), to detect an absolute difference of 15 % in survival free of disability between the two groups at 2 years’ corrected age. The sample size has taken into account a 10 % loss to follow up rate and a disability rate in the control group of 50 %.

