##### Statistical analyses

Statistical analyses will be performed on an intention-to-treat basis. Missing outcome data will not be imputed in the primary analysis, as the key assumption of missing at random is not likely to hold in the analysis population. Sensitivity analyses will be conducted, however, using multiple imputations method to explore the potential impact of missing data on outcomes. The characteristics of those participants with missing data will be compared between two treatment groups. Per protocol analysis will be performed for those who received at least 80 % of the intended treatment. Sub-group analysis will be conducted on the treatment outcomes in relation to total protein received and to the extra study dose received. Statistical tests will be two-sided at a 5 % significance level. Twins will be randomised as separate babies, with the non-independence of these pairs taken into account during analysis.

Baseline characteristics of all randomised babies and their mothers will be summarised for each group as well as overall using descriptive statistics. Continuous variables will be reported as numbers of observed and missing values, mean, standard deviation, median and range. Categorical variables will be described as frequencies and percentages. The primary outcome, survival free of disability, will be first presented as unadjusted relative risk (RR) with 95 % confidence interval (CI). Generalised linear regression models appropriate to continuous and categorical outcomes will be used to evaluate the treatment difference between two groups, adjusting for stratification variables and other baseline confounders that are closely associated with the outcomes (e.g. birth weight, sex and treatment with antenatal steroids). Adjusted RRs and 95 % CIs will be estimated using a log link. Analyses of growth outcomes will be performed following completion of NICU discharge assessments but will not be revealed to assessors of the Bayley III at 2 years’ corrected age.

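### The 24 h consent rule can withdraw a randomised baby who has already died, which conflicts with the intention-to-treat analysis of a survival endpoint

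*Protocol article*

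**What the plan says.** Trial entry and randomisation sets the consent route: "Babies for whom it was not possible to obtain consent antenatally will be enrolled based on a waiver of consent". It closes with the rule at issue: "If consent is not obtained within 24 h of randomisation, the baby will be withdrawn from the study". The rule does not distinguish parents who refuse, parents who have not yet been able to decide, and babies who die before consent could be sought.

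The Aims section describes the study fluid as given "via the UAC starting within 24 h of birth and continued for 5 days". A baby enrolled under the waiver can therefore be randomised and infused before consent is settled.

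The endpoint is defined under Primary outcome: "The primary outcome will be survival free from any neurodevelopmental disability at 2 years’ corrected age". Death is therefore a failure.

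Statistical analyses says "Statistical analyses will be performed on an intention-to-treat basis", with no qualification, and plans to describe every randomised baby at baseline. It adds: "Missing outcome data will not be imputed in the primary analysis, as the key assumption of missing at random is not likely to hold". Multiple imputation is a sensitivity analysis only.

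Participant withdrawal treats stopping the intervention and leaving the trial as different events. On leaving the trial it says: "Consent will be requested to continue to use routinely collected data for study purposes". The triggers it names for leaving are parental request and a decision by the attending physician.

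On attrition, Sample size says: "The sample size has taken into account a 10 % loss to follow up rate". It does not mention withdrawal for lack of consent.

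**The concern.** This is a removal after randomisation, and it can follow exposure to study fluid: up to 24 h of the 120 h infusion, or 24/120 = 20%. A baby who dies without consent inside the window meets the wording of the rule, yet its primary outcome is already known. If the trial holds no permission to use that baby's data, and nothing is imputed, the death is absent from the primary analysis.

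The estimate of a survival endpoint is at stake. Clinical condition and death come after allocation. If the fluid affects very early death in either direction, removing unconsented deaths pulls the estimated effect on early death toward no difference, even with blinding intact. A smaller cost is sample size, because these withdrawals come on top of the follow-up loss that the calculation allows for.

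An analysis plan alone cannot repair this. It cannot analyse data that the consent rule does not let the trial keep.

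**Working it through.** **1. The sections side by side**

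- Trial entry and randomisation: withdrawn from the study, with no exception for death.
- Participant withdrawal: separates withdrawal from the trial from discontinuing the intervention, so the consent rule uses the stronger of the two terms. Its retention of routine data depends on consent, and here the absence of consent is what triggered withdrawal. It does not name the 24 h rule.
- Primary outcome: death settles the endpoint as a failure.
- Statistical analyses: intention to treat, with no imputation in the primary analysis.

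For a baby who dies unconsented, the consent rule applied literally and the intention-to-treat statement cannot both be met.

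**2. The plan's own sample size**

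Inputs from Sample size: 215 per arm, 85% power, two-sided 5%, a 15-point difference, 10% loss, and a 50% control disability rate. The last is read as the control failure rate on the composite, giving 50% v 65% success.

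Pooled formula without continuity correction:

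n = [1.960·√(2·0.575·0.425) + 1.036·√(0.5·0.5 + 0.65·0.35)]² / 0.15² = (1.370 + 0.716)² / 0.0225 ≈ 193.5, rounded up to 194 per arm.

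194/0.9 = 215.6, rounded up to 216 per arm, or 432 in total. This is within 2 babies of the stated 430. At 430 × 0.9 / 2 = 193.5 per arm, power is 85.0%. The stated figure reproduces, and nothing here rests on an error in it.

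**3. Power if a fraction w is also withdrawn for lack of consent**

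The document gives no waiver share or refusal rate, so w is assumed. Analysed per arm = 215 × 0.9 × (1 − w).

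| w (assumed) | babies withdrawn (430w) | analysed per arm | power |
|---|---|---|---|
| 0% | 0 | 193.5 | 85.0% |
| 2% | 8.6 | 189.6 | 84.3% |
| 5% | 21.5 | 183.8 | 83.2% |
| 10% | 43 | 174.2 | 81.1% |

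**4. Bias if the babies removed are early deaths**

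If a fraction d of an arm is removed and all of these are failures, the observed success rate is p/(1 − d). The relative risk is then multiplied by (1 − d_control)/(1 − d_treatment).

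- Equal removal, d = 2% in both arms: 0.50/0.98 = 51.0% and 0.65/0.98 = 66.3%. The difference is 15.3 points and the relative risk stays at 1.30.
- Removal in one arm only, no true effect (50% v 50%): d = 1% gives 0.50/0.99 = 50.5%, a false difference of 0.5 points and a relative risk of 1.01. d = 5% gives 0.50/0.95 = 52.6%, 2.6 points and 1.05.

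Distortion of the relative risk therefore needs deaths before consent to differ between the arms.

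**The case against.** A reader might infer that unconsented deaths will certainly drop out and that the intention-to-treat set is already broken. The document does not support that. It nowhere says that withdrawn babies' data are deleted or left out, and the plan to describe all randomised babies fits keeping them as well as dropping them. A death may count as routinely collected data under Participant withdrawal. Membership of the analysis set is also commonly settled in an analysis plan, which is not shown. What stands against this is narrower: the retention clause needs consent and does not name the 24 h rule, so the literal rule still conflicts with the stated analysis.

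A reader might also infer that the sickest babies are selectively removed and that much of any early harm would be hidden. No figure in the document shows this. The rule reaches only babies without antenatal consent, whose share is not given. Babies in danger of imminent death are excluded at entry, and families and clinical staff are blinded, so allocation cannot directly drive consent. As an illustration, suppose early death is 6% on treatment v 3% on placebo and 55% of early survivors are disability-free. Success per arm is 0.55(1 − e)/(1 − s·e), where e is early death and s the share of early deaths withdrawn. The true difference of −1.65 points becomes −1.19 at s = 30% and −0.86 at s = 50%. The proportion hidden largely restates the assumed s. The shift is 0.5 to 0.8 points, against a standard error of √(0.4775/193.5), about 5 points.

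The power argument is also limited. The loss is small at low withdrawal rates, and part of it is active refusal, which no fair remedy recovers.

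**Conclusion.** The point holds as a conflict between a stated rule and the stated analysis. A baby enrolled under the waiver who dies before consent can, on the literal wording, leave a primary analysis in which its outcome is a known failure.

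Its size cannot be derived from the document. Bias in the relative risk requires removals related to prognosis to differ by arm. If removals are all early deaths and equal in both arms, the relative risk does not change. The power figures rest on assumed withdrawal rates on top of the 10% loss and on reading the 50% disability rate as the control failure rate. On that basis the loss is under 1 point at 2% withdrawn, about 2 points at 5% and about 4 points at 10%.

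It is still worth settling in the protocol, because outcome data that the trial has no permission to keep may not be recoverable later.

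**What to change.** Reconcile Trial entry and randomisation, Participant withdrawal and Statistical analyses:

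1. Seek an ethics-approved extension of the existing waiver so that a baby who dies before consent could be obtained stays in the intention-to-treat set and counts as a primary-outcome failure in its allocated arm.
2. Where consent has simply not yet been obtained, seek permission under Participant withdrawal to use routinely collected data, naming the 24 h rule there. If permission is given, analyse the baby as randomised.
3. Report all babies withdrawn for lack of consent or by refusal, by arm and with timing.

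Consent policy for living babies stays with the ethics committee, and nothing is proposed on the conduct of the study infusion. The sample size need not change, and no extra babies or procedures are needed. The cost is one protocol and ethics amendment, which the committee may not grant in full. Babies whose parents refuse use of data would still be lost.
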